## Abstract

**Background/Objectives:**

The microbiota plays a vital role in the two-way communication between the gastrointestinal tract and numerous neuropsychiatric disorders, such as schizophrenia. Besides, the microbiota modulation through the use of psychobiotics (prebiotics and probiotics with nutraceutical action) is related to the improvement of the physical and psychopathological health. The objective to this study was to test the efficacy of prebiotic/probiotic dietary modulation in patients diagnosed with schizophrenia, attending to the nutritional and cardio-metabolic impact.

**Methods:**

Two-arms, double-blind, randomized in balanced blocks clinical trial of 6 months of intervention, will be developed in a group of 50 individuals. The control group will receive conventional dietary advice individually from specialized mental health nurses. In the intervention group, an individual dietetic-nutritional education program with high prebiotic and probiotic content (dairy and fermented foods, green leafy vegetables, high-fiber fruit, whole grains, etc.) will be developed by these nurses. Data will be collected on the psychopathological state, and blood test (at the beginning, at 3 and 6 months). The estimation of intestinal microbiota and the usual nutritional pattern will also be assessed at the beginning and 6 months, using a stool test. To evaluate the degree of adherence, the intervention group will fill a specific weekly record of the main dishes/food consumed. Anthropometric parameters will also be analyzed monthly.

**Discussion:**

The study is anticipated to establish feasibility an adequate dietary modulation with a high simbiotic content, leads to a significant improvement in the nutritional status and cardio-metabolic. Furthermore, it is presumed to reach a degree of evidence that allows establishing nutritional management as an effective therapeutic intervention in the psychopathological treatment of patients with schizophrenia spectrum disorders.

**Clinical Trial Registration:**

[www.ClinicalTrials.gov], identifier [NCT04366401].

## Background

Schizophrenia is a chronic mental illness characterized by significant clinical heterogeneity and a long evolution over time, determined by periods of psychotic exacerbation and phases of stabilization (1–3). The semiology of this nosological entity is established in positive and negative symptoms, with variable levels of dysfunction and clinical presentation, and having an essential impact on the patient’s quality of life (2, 4). Similarly, surrounding the schizophrenic spectrum, the existence of the associated neurocognitive impairment stands out, prevailing the disorders of social and occupational functioning, as well as a significant degree of disorganization (2, 3, 5, 6).

Many theories have tried to elucidate the origin of schizophrenia, where the complexity of its etiopathogenesis is a determining factor in establishing an appropriate, specific, and effective therapeutic approach (1, 7). In this sense, despite the numerous etiological premises, the glutamatergic (glutamate/GABA) and dopaminergic hypotheses have acquired greater strength in the development of schizophrenia (8, 9). In addition, however, recent studies have highlighted the theory of vagus nerve dysregulation as a possible etiological factor in the origin and aggravation of mental disorders (1, 5, 10), with numerous associated pathogenic mechanisms, particularly low-grade systemic inflammation and oxidative stress (7, 10, 11).

Undoubtedly, the traditional therapeutic approach has perceived the role of nutrition as a minor intervention in psychiatry, especially in psychotic disorders such as schizophrenia (12). However, the advances established in the last decade, mainly associated with the development of the holobionte theory and the evolution of metagenomics (11, 13), as well as the presence of new dietary patterns of low nutritional quality in different western societies (1, 3), have contributed significantly to the global understanding of the role of nutritional patterns on the functioning of the Central Nervous System (CNS), as well as on the possible mechanisms or etiological pathways of psychiatric disorders (1, 11, 12, 14).

In this regard, it is necessary to highlight the role of the intestinal microbiota (IM) and the intimate relationship it exerts on the numerous functions of the body, such as the development and maturation of the CNS, nutrition, immune response or systemic inflammation (7, 11, 12, 15). This effect is carried out through various established communication pathways: vagal nerve (primary), intestinal hormones, cytokines, exosomes, and microRNAs (10, 14–16). Thus, the existence of possible modifications in the concentration of this biota (considering average concentrations around 1,013 CFU/g) (17, 18), may trigger homeostatic alterations or aggravate pathogenic conditions, a fact commonly called dysbiosis (11–13, 17, 19). This concentration of microbiota is fundamentally determined by dietary patterns, genetic factors, iatrogenic antibiotherapy [highlighting the broad-spectrum ones, reducing the potential for small intestinal bacterial overgrowth (SIBO)], type of breastfeeding (maternal or formula), age, exercise, and continuous stress, among others (10, 18–20).

As a consequence of these discoveries, the concept of the “*Microbiota-Intestine-Brain Axis”* emerges. This term refers to the two-way communication pathway established between the CNS, the gastrointestinal tract, and the IM (1, 13–15, 18), mediated by the microbial metabolites of dietary products such as dietary fiber, tryptophan or arginine, as well as by endocrine and neuronal mechanisms (19, 21). The close relationship established between IM and the CNS lies in the production of a multitude of neurotransmitters essential for normal neuronal functioning, such as serotonin, GABA, dopamine or noradrenaline, among others (11–13, 19, 22). Similarly, IM exerts essential trophic, metabolic, and protective functions, which are a determining factor in the normal neuropsychiatric function (17, 22).

Thus, according to the theory of low-grade systemic inflammation, when a state of dysbiosis occurs in the symbiote IM, it generates a cascade of pro-inflammatory agents, such as lipopolysaccharide (10, 11, 23), a bacterial endotoxin, capable of modifying both the integrity and the permeability of enterocytes (12). This alteration triggers the release of pro-inflammatory cytokines [tumor necrosis factor ′α (TNF-′α) or interleukins type 6 or 1β (IL-6, IL-1β) (7, 11), both capable of altering intestinal tissue integrity], originating synergies between inflammation, increased oxidative stress and imbalance of energetic homeostasis. This cascade of reactions causes an increase in neurodegeneration and excitotoxicity, mediated by the vagus nerve (7, 12, 15). Thus, it has been shown that the activation of a state of low inflammation is related to a worse prognosis of schizophrenia concerning positive and negative symptoms, cognitive performance, and loss of brain volume (7, 21, 24). Similarly, alterations in specific pro-inflammatory cytokines or state markers have been described, especially in psychotic relapses or prodromal phases (IL-6, TGF-β, among others) (7, 10), as well as a decrease in their concentration after the introduction of antipsychotic treatment, with consequent clinical improvement (21).

### Justification

Existing scientific production shows a high rate of disability and morbimortality in people suffering from some psychiatric disorder concerning the rest of the general clinical population, especially in those patients with a severe and long-term mental disorder (LTMD) (1, 12, 14, 24–28), highlighting dysfunctions of the psychotic and affective spectrum: schizophrenia and bipolar disorder, (respectively) (24, 27). This morbidity and mortality rate in the psychiatric population is up to 20% higher and, quantitatively, represents an average of 25 years of life lost (24–27, 29). Besides, patients with LTMD have a life expectancy of less than 20% (57 years in men and 65 years in women) (14, 25). It is estimated that the relative risk of this disease is 2.41 higher for mortality from any causes (24), these being mainly comprised of cardiovascular, infectious, respiratory, and endocrine diseases (60% of premature deaths in this clinical population) (14, 25, 30). Also, the leading established causes of mortality are closely linked to the development of the Metabolic Syndrome (MS) (1, 3, 25–28, 31–33), also called insulin resistance syndrome (24, 33). The MS is considered a determining factor in the physical health of the patient, tripling the incidence of cardio-metabolic diseases (27–29).

The main etiopathogenic determinants of this fact are the factors inherent to the disease itself, as well as genetic factors (3, 24–26, 34) and resistance to adequate care in terms of physical health (27, 33, 35). However, the main modifiable risk factor in the LTMD population lies in the acquisition of unhealthy lifestyles, characterized by high-energy dietary patterns, with high consumption of ultra-processed foods and low fruit and vegetable intake (36). In addition, the psychiatric population has low levels of physical activity, with increased rates of smoking and associated substance abuse (3, 27, 37, 38).

Despite the magnitude and severity of the problem, interventions aimed to modify lifestyles do not play an essential role in therapy and are not part of the usual clinical practice with the psychiatric population (1, 27, 31, 33). This fact could be explained by the lack of understanding of the multiple mechanisms and etiological factors involved in the neurogenesis of schizophrenia (2), and leads to a multidisciplinary approach, but essentially psychopharmacological and psychotherapeutic (33, 39). It is, therefore, vital to address modifiable factors such as dietary patterns, which have evidenced to be an efficient therapeutic intervention to improve both the psychopathological dysfunction and the physical health of the subjects and can be considered as an addition to the conventional therapeutic approach (1, 3, 7, 17, 40).

In this sense, some dietary interventions carried out to modulate intestinal microbiota in psychotic disorders through the use of so-called “psychobiotics” (1, 17–22). This term refers to the set of substances that include probiotics and/or prebiotics and whose administration causes health benefits in psychiatric patients (20–22). Probiotics include microorganisms of the intestinal biota, which, provided in adequate quantities, offer a benefit for the host (highlighting the genera Lactobacillus and Bifidobacterium, among others) (1, 7, 8, 12, 16–21). On the other hand, prebiotics are non-digestible dietary fiber (mainly fructooligosaccharides and oligosaccharides, inulin or pectins) (1, 17), which are substances that promote optimal growth and development of probiotics in the gastrointestinal tract, reducing pathogenic microbiota (7, 12, 15, 19), through the production of short-chain fatty acids (17, 21).

It is worth noting the growing effort to highlight the role played by prebiotics and or probiotics in the microbiota-intestine-brain axis, which is currently a relevant object of study (1, 22, 41).

In this regard, according to Patra (19) and Teasdale et al. (37), adequate dietary planning in psychiatric patients with psychopathological dysfunction and at risk of iatrogenic metabolic syndrome, could be considered as a therapy of choice in these subjects, improving altered clinical patterns and difficulties in the patient’s vital and functional performance. Similarly, adequate nutritional management could be used as an adjunct to antipsychotic pharmacotherapy and the cardio-metabolic approach, reducing the number of homeostatic drugs or even replacing them in cases of intolerance in the target population (14, 39).

In short, the future of the development of Mental Health is determined by the need for a multimodal approach, where nutritional factors represent the cornerstone in achieving optimal results in health, level of functionality, and, therefore, quality of life of patients (35, 42).

Likewise, dietary advice on modulation with high prebiotic and probiotic content has the added value of improving the morbidity and mortality associated with schizophrenia, with optimal levels in terms of cost-effectiveness, better than those shown by the approaches currently used.

## Methods/design

### Study aims

#### Main objective

Determination of the nutritional and cardio-metabolic efficacy of a prebiotic and probiotic dietary intervention in patients with schizophrenia spectrum disorders.

#### Specific objectives

-To determine the baseline nutritional status of the target population.-To identify the usual dietary patterns in this population, clarifying the nutritional value of the main dishes consumed, as well as their link with the physical health status of individuals.-To know the existing scientific evidence regarding the construction of determinants (explicit and implicit) that influence the microbiota-intestine-brain axis.-To evaluate the psychopathological impact of the incorporation of prebiotics and probiotics in the habitual dietetic-nutritional pattern in patients diagnosed with the spectrum of schizophrenia.-To evaluate the cardio-metabolic impact of a standardized dietary planning with high prebiotic and probiotic content, adapted to the inherent characteristics of the psychiatric population.-To develop and validate a program that allows for the detection of areas of improvement, establishing assessment strategies, and an appropriate action plan in Mental Health, which allows for adequate dietary care through the use of psychobiotics.

### Study design

A two-arms, double-blind, randomized in balanced blocks clinical trial of 6 months of intervention, will be carried out in psychiatric patients diagnosed with schizophrenic spectrum disorders (without distinction by type). The control group (CG) will be made up of those participants who will receive conventional dietary advice (43) on an individual basis. In the intervention group (IG), this advice will be established individually through intensive nutritional guidance (44) offering a food pattern with a high prebiotic and probiotic content. In both intervention groups, educational material of visual support will be used during the sessions. The dietary intervention will be designed and supervised by qualified personnel with recognized competencies for this intervention (nurses and dietitians), carried out by specialized mental health nurses, and will be agreed upon through serial interviews and focus groups. In this sense, these focus groups will be applied to improve the established dietetic-nutritional intervention, guaranteeing its correct adaptation, according to the study population.

The study will begin with a group session for the presentation of the research project in the health center and/or psychiatric service consultation. During the development of the study, data will be collected on the psychopathological state [Positive and Negative Syndrome Scale (PANSS) (45) and Personal and Social Functioning Scale (PSP) (46) scales; Supplementary Tables 1, 2], and blood test (hemogram, lipid profile, etc.). Measures will be taken at the beginning (basal), at 3 and 6 months. The estimation of intestinal microbiota and the usual nutritional pattern will also be assessed at the beginning and 6 months, using a stool test and a validated Food Frequency Questionnaire (FFQ) (47), respectively. The use of the FFQ will allow us to know both the average intake of grams of fiber, fat, etc. and the frequency of consumption by food groups (with particular attention to fermented foods). However, the main reason for using this tool is that it will allow us to assess changes in dietary patterns over the medium term (39). To evaluate the degree of adherence, participants in the IG will fill a specific weekly record of the main dishes/food consumed with a high prebiotic and/or probiotic content will be measured by the weekly completion (during the 6 months of intervention) of a record that includes the main foods consumed with a high symbiotic value (fermented foods, whole grains, green leafy vegetables, fruit, etc.) (Supplementary Figure 1). This record will be completed by the patients themselves or, in cases of incapacity or lack of autonomy in preparing the dishes consumed by family members or the primary caregiver. At least, anthropometric parameters will also be analyzed monthly (BMI, blood pressure, heart rate, abdominal perimeter) (Supplementary Table 3).

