### Work plan

An intervention schedule has been established, with a total duration of 6 months, which is divided into three blocks:

#### Block 1

This first block focuses on the selection of the target population according to inclusion criteria. Firstly, a group session to present the program and the methodology of the study will be carried out. During the first 15 days of the study, a focus group with professionals to reach a consensus on the intervention will be held. Subsequently, the appropriate modifications will be made to improve and adapt to the dietary and nutritional intervention.

Consequently, the recruitment and initial psychopathological and nutritional assessment of the participants will be carried out, using the PANSS (45) and PSP (46) scales. For the nutritional evaluation, the analytical and anthropometric basal determination of the participating patients will be carried out, as well as the evaluation of the habitual dietary pattern through a validated FFQ (47) and weekly record of the main dishes and foods consumed. Similarly, an estimate of the intestinal bacterial flora is required employing stool culture.

#### Block 2

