The second block includes the implementation of the 6-month individual nutrition education program (associated with 2 months of educational reinforcement, according to block 3). It will consist of eight sessions, the first four being biweekly, followed by 4 monthly, to which four sessions of educational reinforcement will be added to the 3 and 5 months of study. The minimum duration of each session has been established for 30 min. However, this length could be different, considering the characteristics of the participants. The control group will be made up of those participants who will receive standardized dietary advice (35). In this sense, the education content in the intervention group will be based on general principles of conventional dietary advice in an intensified manner (36), centered on the acquisition of specific knowledge about: (I) Underlying mental pathology, lifestyles and associated comorbidities; (II) Immediate principles: Carbohydrates, lipids, proteins, fiber, vitamins, and minerals; energy needs; consumption requirements; (III) Water requirements; (IV) Foodstuff; (V) Description and justification of prescribed prebiotic and probiotic diet; (VI) Culinary techniques: conservation of properties of the prebiotic and probiotic diet; (VII) Optimal distribution and interchange of foods with high prebiotic and probiotic content; (VIII) Feeding in particular situations.

In both the IG and the CG, visual support resources will be used during the development of the established sessions.

#### Block 3

Finally, to evaluate the effectiveness of the intervention, the modification in the nutritional, the cardio-metabolic, and the psychopathological area will be assessed. For doing this, researchers will carry out anthropometric determination, clinical evaluation, the performance of stool culture, and the study of the dietary pattern, as we commented above.

Likewise, in this block, an educational reinforcement (both in IG and CG) of what was treated in Block 2 will be offered, 3 and 5 months after the beginning of the block, every 15 days for the IG and monthly for the CG.

Once the intervention is concluded, the analysis of the collected data will be performed, culminating in the development of the scientific production and the writing of the research report.

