## Discussion

Firstly, it is expected to obtain the necessary information for the determination of the optimal dietary pattern for those participants in the study, thus allowing the development of a nutritional intervention with high prebiotic and probiotic content, appropriate for the population under study.

Likewise, the aim is to ensure that all participants improve their health status through the adaptation of the feeding pattern, developing adherence to healthier lifestyles adapted to the conditions of each patient.

Finally, it is expected to demonstrate that an adequate dietary modulation with a high prebiotic and probiotic content, leads to a significant improvement in the nutritional status and, therefore, the cardio-metabolic, of the participants, mediated by the microbiota-intestine-brain axis. Furthermore, it is presumed to reach a degree of evidence that allows establishing nutritional management as an effective therapeutic intervention in the psychopathological treatment of patients with schizophrenia spectrum disorders, in any of its variants.

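### The trial is labelled double-blind, but the nurses who teach and the intervention participants must know the arm; the food questionnaire is therefore unblinded, and no masking of the PANSS and PSP raters is stated

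*Protocol article*

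**What the plan says.** The label appears twice in the protocol article: in the Abstract ("Two-arms, double-blind, randomized in balanced blocks clinical trial of 6 months of intervention") and under Study design ("A two-arms, double-blind, randomized in balanced blocks clinical trial of 6 months of intervention"). Neither place names the blinded parties, and no masking procedure is described elsewhere.

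The same article describes delivery and outcomes as follows.

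- **Who teaches.** Specialised mental health nurses give controls conventional dietary advice. The intervention programme "will be developed by these nurses" (Abstract, Methods).
- **What intervention participants are told.** The Block 2 curriculum in the Work plan includes "Description and justification of prescribed prebiotic and probiotic diet".
- **What intervention participants record.** "To evaluate the degree of adherence, participants in the IG will fill a specific weekly record of the main dishes/food consumed" (Study design). The record covers foods of high symbiotic value and runs through the six months.
- **Contact.** Block 3 reinforcement is "every 15 days for the IG and monthly for the CG".
- **Opening session.** In Block 1, "a group session to present the program and the methodology of the study will be carried out".
- **Placebo.** Limitations explains that the nurses cannot prescribe symbiotic formulas or manage a placebo.
- **Outcomes.** Study variables lists PANSS and PSP under clinical efficacy and the food frequency questionnaire (FFQ) under dietary pattern. Block 3 assigns the final anthropometry and clinical evaluation to researchers and does not say whether they are masked.
- **Expected conclusion.** The Discussion expects nutritional and cardio-metabolic improvement "mediated by the microbiota-intestine-brain axis".

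**The concern.** A reader takes double-blind to mean that at least the participants and the people treating them do not know the allocation. Results on self-reported and rated scales are trusted more for that reason. If the label is wrong, the FFQ is credited with protection it does not have, and PANSS and PSP may be as well.

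The FFQ is the most exposed. Participants who have been taught which foods to eat report how often they eat them, and the article says fermented foods will get particular attention. The likely bias favours the intervention arm.

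The arms also differ in contact and self-monitoring. A positive result could come from these rather than from prebiotic or probiotic content acting through the gut–brain axis.

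**Working it through.** The blinding claim has no figure to reproduce, so the main check sets the article's statements side by side.

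**Step 1. Can each party be blind under the described design?**

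| Party | What the article describes | Can be blind? |
|---|---|---|
| Nurses who teach | Conventional advice in one arm, an intensive prebiotic/probiotic programme in the other | No. Whoever teaches a curriculum knows which one it is, whether or not one nurse covers both arms |
| Intervention participants | Taught the diet and its rationale; keep a six-month record of target foods; no placebo or masked product | No |
| Control participants | Individual advice with visual material; reinforcement sessions; opening group session | Not established either way |
| Raters and measurers | Described only as researchers | Not stated |
| Laboratory, analyst | Not described | Not stated |

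The first two rows contradict the label. The others are open.

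**Step 2. Does the recording difference stand?** Block 1 mentions a weekly food record at the baseline assessment without limiting it to an arm, so controls may complete one at the start. The Abstract and Study design assign the six-month adherence record to the intervention arm only. The difference during follow-up therefore stands.

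**Step 3. Which outcomes are exposed?**

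- FFQ: self-reported by participants who, in the intervention arm, know what they were taught. Masking a rater cannot protect it. It bears on the main objective, which is nutritional and cardio-metabolic efficacy.
- PANSS, PSP, waist and blood pressure: exposed if the assessor knows the arm. The article does not rule this out.
- Blood and stool values: much less open to reporting or rating bias, though unequal contact can still affect them.

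**Step 4. Illustration of size.** The bias size is an assumption; nothing in the documents supplies it. Take no true effect, a two-sided t-test at 5%, n per arm, and a pure bias of b SD. The test statistic then follows a noncentral t distribution with 2n − 2 degrees of freedom and noncentrality b × √(n/2). The false-positive rate is the probability that it exceeds the critical value in either direction.

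- n = 25 (planned per arm): 48 df, critical value 2.011.
  - b = 0.2: noncentrality 0.2 × √12.5 = 0.707, rate 10.7%.
  - b = 0.3: noncentrality 0.3 × √12.5 = 1.061, rate 18.0%.
- n = 11 (the article's calculated minimum per arm, used here as a heavy-dropout case): 20 df, critical value 2.086.
  - b = 0.2: noncentrality 0.2 × √5.5 = 0.469, rate 7.3%.
  - b = 0.3: noncentrality 0.3 × √5.5 = 0.704, rate 10.3%.

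Under these assumptions the range is about 7% to 18%, against a nominal 5%.

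**The case against.** The best defence is that the article condenses a fuller protocol, which may mask raters or analysts. That is possible, and it is why no failure of PANSS or PSP masking can be asserted here. But such masking would support the term assessor-blinded. It would not make the nurses or the intervention participants blind, and it would not protect the FFQ.

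Three further objections hold and limit the point.

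- **Control participants.** A reader might infer that nobody in the trial can be blind. The documents do not show this for controls. Both arms get individual advice, visual material and reinforcement, and nothing says that the opening session discloses what each arm is taught.
- **The same nurses.** A reader might infer that each nurse teaches both arms. The Abstract's wording can equally mean the professional category, and no section assigns individuals to arms. The conclusion does not need that inference.
- **Scope.** Much of the main objective rests on blood values and measured anthropometry, which are less exposed than self-report. Limitations already frames the trial as a test of a health-education strategy, and extra intensity is part of that strategy. Unequal contact is then not a flaw in comparing the packages. It is a reason not to attribute the effect to the microbiota. The mediation phrase is an expectation in the Discussion, and the Statistical analysis section plans no mediation analysis.

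It may also be tempting to ask that controls keep the same record of symbiotic foods, or that the efficacy claim move to HbA1c or lipids. Neither follows. The first would show controls the target foods and risk contamination. The second would change the endpoint with no check of power.

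**Conclusion.** The concern holds in a limited form. As written, double-blind contradicts the article's own account of delivery for two parties: the teaching nurses and the intervention participants. That rests on the text alone. The FFQ is therefore unblinded self-report. PANSS, PSP and the measured anthropometry are exposed unless their assessors are masked, which the article does not state.

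The documents do not support the stronger readings that controls are certainly unblinded, that the ratings are certainly biased, or that the laboratory results are compromised by reporting.

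No size of bias can be derived from the documents. The 10.7% to 18.0% false-positive range assumes a 0.2 to 0.3 SD bias and 25 completers per arm. With 11 per arm it is 7.3% to 10.3%. These figures are illustrative, and the contradiction stands without them. It needs correcting because the label is a core design statement on which readers judge the risk of bias.

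**What to change.** 1. Remove double-blind from the Abstract and Study design, and state who is masked and how.
2. Have PANSS, PSP, waist and blood pressure assessed by existing team members who do not teach that participant and cannot see the food records. Call the trial assessor-blinded only if this is done.
3. Label the FFQ as unblinded self-report wherever its results are presented.
4. Add open delivery and the unequal reinforcement contact (every 15 days against monthly) to Limitations.
5. Word the conclusion as the education package against conventional advice, in line with what Limitations already says, and drop the statement that the effect is mediated by the gut–brain axis.

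**Cost.** Text edits, a rota change among existing staff, and a weaker design label. Sample size, endpoints and the content of either arm stay as they are.
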